### Process evaluation

A combination of questionnaires, interviews, and field observations will be used to assess the process. The purpose of process assessment is to understand: participants' different experiences of intervention measures; any differences between expected and observed results; sustainability of intervention programs; possible contamination between the intervention group and the control group; and any unexpected events in the process that are not part of the results of the study.

Attendance at communication campaigns will be recorded. Each cluster will have a special person to check intervention measures implementation. All activity processes will be recorded. In case of important modifications, they will be explained to the experimental participants in accordance with relevant regulations and agreed, and the modifications will be made in the trial registration center at the same time. After each follow-up, the project researchers will analyze the data and report the results to the PI. During the experiment, when force majeure fails to continue intervention or other situations must be terminated, the PI will make the final decision to terminate the trial.

### Oversight and monitoring

#### Composition of the coordinating center and trial steering committee

Ningxia Medical University will serve as the coordination center. In view of the low risk associated with this study, no independent trial steering committee will be established for this study.

#### Composition of the data monitoring committee, its role, and reporting structure

The School of Public Health of Ningxia Medical University will independently monitor the data. They are responsible for verifying the qualifications of the participants, the written informed consent, compliance agreements, and the accuracy of the data collected. Only investigators and members of the data center will have access to anonymous data.

### Ancillary and post‑trial care

Although the team in this study aims to mitigate the risks associated with the intervention, minor harm may nonetheless occur. Compensation is not provided for participants who are injured in this research project. In case of injury, participants will be advised to contact Ningxia Medical University's Ethics Committee.

### Frequency and plans for auditing trial conduct

The Project Management Group meet to review trial conduct once a month. The independent Data Monitoring and Ethics Committee meet to review conduct throughout the trial period. An independent party will audit and report the results.

### Plans for communicating important protocol amendments to relevant parties

Any protocol modifications will be reviewed by Ningxia Medical University and then revised in the Chinese Clinical Trial Registry. All relevant information will be shared among researchers.

### Dissemination plans

The results of this study will be published in peer-reviewed journals.

### Patient and public involvement

In the design stage of the study, we gathered the older people over 60 years old to discuss which leisure activities are more appropriate, and discussed what kind of outcome indicators could be collected. This has a positive effect on the formulation of our protocol. In addition, during the study, researchers will visit the site regularly and adopt diversified methods to obtain the opinions of the research objects, improving the public’s and participants’ engagement throughout the study process and disseminating the findings.

## Discussion

With the increase in age, the probability of cognitive impairment in the older people is on the rise [42, 43]. More and more evidence shows that participating in cards and chess leisure activities is beneficial to the cognitive and psychiatric state of the older people [18, 19]. Although previous cross-sectional or cohort studies have shown beneficial prospects for leisure activities [44, 45], the quality of the study design is low. Many previous studies have not fully considered baseline cognitive state and other confounding factors, both of which may lead to bias, and no effective cluster randomized controlled trials are underway. Advantages of this study include robust randomized controlled trial design, randomization at the cluster level to reduce contamination, large population, including medium-term and long-term follow-up measures, and strict objective scale measurement as the main results. In addition, the uniqueness of this study is that it will clarify the influence of the frequency and duration of participation in chess and cards activities on cognitive function. Inevitable limitations of this study include: First, due to the nature of this study, participants cannot turn a blind eye to the interventions they receive, and if researchers interact with subjects, they cannot keep blind to researchers, which may lead to information bias. Second, basic information, the duration and frequency of leisure activities are reported by the subjects themselves, which may lead to recall bias. Nevertheless, the present study will fill gaps in the literature. This study will help to build an evidence base around the effectiveness of interventions to reduce cognitive impairment in the older people, and provide valuable information for successful aging.

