**Discussion:**

The results of this RCT will be helpful to (1) confirm the effectiveness of chess and cards leisure activities in improving the cognitive function of the older people over 60 years old; (2) determine the relationship between the frequency and duration of chess and cards leisure activities and cognitive function; (3) provide evidence of promoting participation in leisure activities through education campaigns and free provision of chess and cards tools; and (4) provide valuable information for successful aging.

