Although previous studies have provided a great deal of epidemiological reference information about the association of leisure activities with cognitive function, the epidemiological evidence linking specific leisure activities with reducing cognitive decline is not enough to indicate whether these activities have any direct preventive or delaying effects. So far, the evidence from randomized controlled trials supporting the cognitive benefits of leisure activities in the older people through chess and cards is still limited. Most research designs are cross-sectional studies [25] or longitudinal studies [26], and causal inferences cannot be made. Individual randomized controlled trials with a small sample size on cognitive leisure activities are limited to cognitive impairment samples [27, 28]. Therefore, intervention research is needed to prove the causal relationship between chess and cards leisure activities and cognitive function in the population, and to verify whether chess and cards leisure activities are an effective non-drug treatment for the older people. In recent years, social media have been a source of information about cognitive impairment prevention and treatment. This is because massive promotion campaign is also one of the most important aspects of health work. We expect the elderly to voluntarily give up problematic living habits and adopt active lifestyles to delay the decline of cognitive function after being advertised.

Furthermore, there is no single, large-scale, and robust design study to measure the cognitive intervention effect of free chess and cards leisure activities on the older people. To solve this problem, we designed a more convenient and economical cluster randomized controlled trial to avoid contamination and evaluate the real effect of the intervention. We aim to maximize the potential health benefits of chess and cards activities for the older people through intervention. We will not only pay attention to communication campaigns, but also the availability of tools (chess and cards), and improving the activities and atmosphere.

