### Intervention group

Each participant in the intervention group will be given personalized chess and cards leisure activities tools (chess, military chess, gobang, checkers, poker, long cards, etc.) according to their preferences. In addition, we provide education campaigns on the prevention and treatment of cognitive impairment for all residents in the village. Promotion is achieved by publishing relevant popular science content on the village's social platform. Every month, the fixed host convenes the whole village over 60 years old to give a lecture on cognitive impairment prevention. Education focuses on leisure activities and their benefits. Participants are encouraged to plan their leisure time reasonably and take the initiative to participate in various leisure activities, especially social leisure activities such as playing cards and chess. The recommended frequency of chess and cards activities is 5–6 times a week, for at least 1 h. Each village will appoint a responsible person and receive training to motivate their neighbors to actively participate in chess and cards leisure activities. Social support from neighbors and family members will be encouraged through participation in regular activities inside and outside of life. The intervention time was 2 years.

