#### Self-reported chess and cards leisure activities

Participants will be asked to complete a questionnaire on their participation in chess and cards leisure activities. They will also be asked to estimate the frequency and duration of their participation in chess and cards leisure activities. Information on sleep duration and quality, smoking status, drinking status, and exercise status will also be collected through self-reports.

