### Assignment of interventions: allocation

#### Sequence generation

In this cluster randomized controlled trial (RCT), 8 villages will be recruited. A village is a cluster. To reduce contamination risk, clusters will be randomized at the village level. Using a computer-generated list, statisticians at Ningxia Medical University randomly assigned villages (clusters) to one of the two groups and stratified them according to the counties to which villages belong before allocation. The randomization will be performed using a computer-generated randomization table in Microsoft Excel.

Randomization will be carried out after the cluster completes the baseline measurement. These clusters will be recruited from Helan County, Litong District, Qingtongxia City, and Shapotou District in Ningxia, China. Our goal is to recruit 800 over-60 s in 8 clusters. Clusters will be randomly assigned to accept one of the following conditions: (1) intervention groups that distribute leisure activities tools (chess and cards) free of charge and promote them, or (2) control groups (routine).

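### The Discussion promises to show the influence of how often and how long people play, but dose is self-chosen and not randomised, so the trial can describe only an observational association

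*Protocol article*

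**What the plan says.** The Discussion, after listing the randomised design among the study's advantages, says the study is unique in that "it will clarify the influence of the frequency and duration of participation in chess and cards activities on cognitive function". The Discussion part of the Abstract gives a softer version as the second expected result: "determine the relationship between the frequency and duration of chess and cards leisure activities and cognitive function".

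Four other places bear on whether the design can deliver this.

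- **What is randomised** (Sequence generation): "clusters will be randomized at the village level". No level of play is allocated.
- **How dose arises** (Intervention group): tools are handed out by preference and there is a single recommendation, "The recommended frequency of chess and cards activities is 5–6 times a week, for at least 1 h". Beyond that, "Participants are encouraged to plan their leisure time reasonably and take the initiative to participate in various leisure activities".
- **How dose is measured** (Self-reported chess and cards leisure activities): "They will also be asked to estimate the frequency and duration of their participation in chess and cards leisure activities".
- **What is conceded** (Discussion): "the duration and frequency of leisure activities are reported by the subjects themselves, which may lead to recall bias". Self-selection, confounding and reverse causation are not mentioned for the dose question.

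The article's own standard for non-randomised evidence is in the Background: "Most research designs are cross-sectional studies [25] or longitudinal studies [26], and causal inferences cannot be made".

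Statistical methods describes one exposure, the randomised arm. Secondary objectives lists frequency and duration of play among the things the intervention is meant to change, not as an exposure. No dose model is described.

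**The concern.** Everyone in an intervention village is offered the same package, and the differences in dose between them come from their own choices. People who play more may differ in education, health, sociability and cognition before they start. People whose cognition slips may play less, or report their play less accurately. A comparison of heavy with light players is then a cohort comparison nested inside a trial, and randomisation of villages does not protect it.

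At stake is what the trial may conclude. A finding about how often and how long to play would be read as a result of a randomised trial when it has only the standing of the studies the article set out to improve on. The Discussion faults earlier work for not fully considering baseline cognition and other confounders, but does not apply that criticism to its own dose claim.

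**Working it through.** The article gives no figure for the dose claim, so there is none to reproduce. The logic is settled by the passages above: allocation is by village, dose is chosen and reported by the individual, and the Background rules out causal inference from such data. The arithmetic below only shows how large an artefact could be.

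**Inputs from the document:** one arm of 4 × 100 = 400 people and two-sided 5% (Sample size). **Assumptions, not in the document:** 12-month autocorrelation of cognition 0.7; correlation *r* of current play with current cognition 0.1 to 0.3, arising only because cognition drives play; error-free score unless stated; clustering ignored; true effect of play zero.

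**Concurrent play, adjusted for baseline.** Let C0, C1 and C2 be standardised cognition at 0, 12 and 24 months, and P2 = r·C2 + noise, with variance 1.

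- corr(C0, C2) = 0.7² = 0.49, and 0.49² = 0.2401.
- Partial correlation of P2 and C2 given C0: ρp = r·√0.7599 / √(1 − 0.2401·r²).
- λ = √397 · ρp / √(1 − ρp²); rejection ≈ Φ(λ − 1.96) + Φ(−λ − 1.96).

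| r | ρp | λ | Formula | Simulated |
|---|---|---|---|---|
| 0.1 | 0.0873 | 1.75 | 42% | 42-43% |
| 0.2 | 0.1752 | 3.55 | 94% | 92-95% |
| 0.3 | 0.2644 | 5.46 | >99% | 100% |

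Varying autocorrelation from 0.5 to 0.85 and score reliability from 0.8 to 1.0, the simulated rates were 24-49% at r = 0.1, 72-98% at 0.2 and 98-100% at 0.3.

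**The rate depends on the model.** With 12-month play P1 adjusted for baseline only, ρp = 0.357·r / √(0.7599·(1 − 0.49·r²)), where 0.357 = 0.7 × (1 − 0.49). This gives 0.041 (λ = 0.82, 13%) at r = 0.1 and 0.083 (λ = 1.65, 38%) at r = 0.2; simulation gave 14% and 37%. With 12-month play adjusted for baseline and 12-month cognition, P1 depends on cognition only through C1, so its partial association with C2 is zero and the rate is nominal (simulated 4-6%).

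**A different set-up** ties play to baseline cognition and, optionally, to later decline (n = 400, SD 2, no effect of play; 1,000 runs per setting). Rejection rates for 24-month score on play:

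| Correlation with baseline cognition | Unadjusted | Baseline-adjusted, no error | Baseline-adjusted, reliability 0.8 |
|---|---|---|---|
| 0.1 | 42-49% | 5% | 10% |
| 0.2 | 93-97% | 5% | 19% |
| 0.3 | 100% | 4% | 40% |

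If decliners also play less (assumed path 0.2), the baseline-adjusted rate is 35-77%. Baseline adjustment is therefore enough only if the score is error-free and play is unrelated to later decline.

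**Measurement error also affects the lagged model.** With reliability 0.8, simulation of 12-month play adjusted for baseline and 12-month score gave about 6-8% at r = 0.2 and 9-19% at r = 0.3. As a check at autocorrelation 0.7 and r = 0.2, the observed-score correlations are 0.8 × 0.7 = 0.56 (12 months apart) and 0.8 × 0.49 = 0.392 (24 months apart). Play correlates √0.8 × 0.2 = 0.179 with the 12-month score and 0.7 × 0.179 = 0.125 with the other two. The partial correlation is 0.027, λ ≈ 0.55, and the rate is about 8%.

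**The case against.** The strongest reply is that the article states no dose analysis. The only model described has the randomised arm as exposure, and an article may leave dose modelling to a fuller document. The 42% and 92-95% figures belong to a concurrent-play model the authors never chose. Play is also assessed at 12 months, so a lagged analysis is equally open to them, and other specifications give far lower rates. The Abstract's wording is close to neutral, and frequency and duration as outcomes of the intervention are a legitimate randomised comparison.

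Most of this stands. The absence of a dose model is not a fault, and the simulated rates are illustrations. What survives is the printed claim: no later analysis plan can make a self-chosen dose randomised.

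A reader might go further and infer three things the document does not support.

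- *That a null effect would certainly look like a dose-response.* Nothing in the article says that better cognition leads to more play. It is plausible, but assumed here. The exclusion of diagnosed dementia, inability to communicate and loss of daily living ability narrows the group in whom it would be strongest, though decline during follow-up remains.
- *That the authors plan to regress 24-month cognition on 24-month play.* They do not say so.
- *That the primary result is compromised.* The primary objective and the arm comparison do not use dose.

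**Conclusion.** The point holds as one about what the trial may claim. The Discussion attributes to the trial a property its design lacks: evidence on the influence of dose, when dose is neither assigned nor independently measured, and only recall bias is admitted. By the Background's own standard, such a comparison does not allow causal inference.

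The possible size of a false dose-response cannot be fixed from the document. It runs from nominal to near certain, depending on the assumed link between cognition and play, the reliability of the score and the model used. Correlations of 0.1 to 0.2 are enough to matter if concurrent play is used. The correction is worth making because it limits a headline conclusion; it does not touch the primary analysis.

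**What to change.** - In the Discussion, replace the promise to *clarify the influence* of frequency and duration with one to *explore the observational association*. Read the second expected result in the Abstract the same way.
- Add self-selection, confounding and reverse causation to the limitations, beside recall bias.
- Reserve causal statements for the comparison of arms as randomised.
- If a dose analysis is done, relate 24-month cognition to play reported at 12 months, adjusted for baseline and 12-month cognition, baseline play, education and health, with the village random effect. Do not use concurrent 24-month play as the exposure. Report it as exploratory.

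The cost is a few sentences and, at most, one extra model on data the article already plans to collect. The downsides are that the advertised unique contribution becomes weaker, only second-year change informs the lagged model, and residual confounding from measurement error remains (the 6-8% and 9-19% above). The lagged model therefore supports the wording change and cannot replace it.

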### Trial status

The recruitment time of this study is from March to June 2023. The anticipated period is 24 months, and the study is expected to be completed in June 2025.

## Data Availability

Data will be made available after the main trial analyses have been completed on reasonable request from researchers with ethics approval and a clear protocol. The informed consent form is in Chinese, and the relevant materials of informed consent are available, on request, from the corresponding author.

## Abbreviations

RCT: Randomized controlled trial
MCI: Mild cognitive impairment
CONSORT: Consolidation Standards of Reporting Trials
KABP: Knowledge-Attitudes-Belief-Practice
MMSE: Mini-Mental State Examination
MoCA: Montreal Cognitive Assessment
AD: Alzheimer’s disease
ADL: Activities of daily living
PSMS: Physical Self-Maintenance Scale
GDS: The Geriatric Depression Scale
SAS: Self-rating Anxiety Scale
